## Abstract

Background: Dentine hypersensitivity on an exposed root surface induces pain, affects daily oral hygiene practice, limits dietary choices and negatively affects quality of life. Silver diamine fluoride is marketed in the United States as a desensitising agent, but well-designed clinical trials are limited. This study evaluates the anti-hypersensitivity effect of silver diamine fluoride on hypersensitive teeth due to an exposed root surface in older Chinese adults. Methods/design: We will conduct a randomised double-blind clinical trial with a sample size of at least 148 Chinese older adults aged 65 or above who have dentine hypersensitivity due to an exposed root surface. We will collect written consent before the study. A trained examiner will examine the participants’ teeth with a blast of compressed air from a 3-in-1 syringe. Those adults who report a self-perceived sensitivity score (SS) (0 to 10) of 8 or more on at least one tooth with an exposed root surface will be recruited. The recruited older adults will be randomly allocated into two groups using a block randomisation of six. Group 1 participants will receive the application of 38% silver diamine fluoride solution every 4 weeks. Group 2 participants will receive the application of 5% potassium nitrate solution every 4 weeks. Dietary advice, oral hygiene instruction and fluoride toothpaste at 1450 ppm will be provided to participants in both groups. The same trained examiner will perform follow-up examinations for the participants and determine the dentine hypersensitivity in SS of the most hypersensitive tooth (with the highest pre-treatment SS) immediately after the intervention and at 4-week and 8-week intervals. Discussion: There is no consensus on the standard of care for a professionally applied desensitising agent in older adults. This trial will provide evidence for clinicians to devise an effective dental care plan for older adults with dentine hypersensitivity. Trial registration: NCT05392868 Registered on 22 May 2022.

## 1. Background

Caries, periodontal disease and tooth wear are the most common dental problems in older adults [1]. They are the typical causes of dentine hypersensitivity. In 2012, the prevalence of dentine hypersensitivity was 35% among the general population in China, with 38% in older adults aged 60–69 [2]. In 2011, almost half (48%) of the non-institutionalised older adults aged 65–74 in Hong Kong suffered from dentine hypersensitivity [3]. Dentine hypersensitivity is characterised by sharp, short-lasting pain originating from the pulpal tissues in healthy pulp resulting from a stimulus, which can be thermal (hot or cold), electrical, mechanical, osmotic (sweet or sour) or chemical [4]. The mechanism of dentine hypersensitivity is unclear; however, the most common proposed theory is the hydrodynamic theory. The theory suggests that changes in the fluid flow in dentinal tubules due to changes in temperature and air pressure cause hypersensitivity. The fluid movement triggers pain receptors at the nerve endings located at the pulpal aspect to elicit nerve impulses, thereby inducing pain [5]. People who perform an incorrect tooth-brushing technique, have periodontal disease or have recently received periodontal therapy are at risk of developing dentine hypersensitivity [6,7]. Dentine hypersensitivity induces pain and affects the daily oral hygiene practice, which further jeopardises periodontal health [8]. It also limits dietary choices and negatively affects quality of life [8,9].

Managing dentine hypersensitivity begins with obtaining the correct diagnosis through history taking and clinical examination [10]. The aetiological factors should then be addressed by providing proper oral hygiene instruction and dietary advice [10]. The use of desensitising agents can relieve pain. Two modes of treatment action of desensitising agents exist. The first one is by occluding the dentinal tubules; the second is by modifying or blocking the pulpal nerve response [11]. Desensitising agents can be self-applied daily or professionally applied at regular intervals. Desensitising toothpaste incorporated with potassium nitrate is a convenient self-applied method. This treatment effectively manages dentine hypersensitivity; however, it often takes 4–8 weeks to achieve pain relief [11,12]. Clinicians can apply desensitising agents on exposed dentine regularly. Several agents are available, such as sodium fluoride varnish and silver diamine fluoride (SDF) solution [12]. However, there is limited evidence on the clinical efficacy of using professionally applied desensitising agents in reducing dentine hypersensitivity [11].

In 1974, potassium nitrate was introduced as a desensitising agent for in-office therapy to manage dentine hypersensitivity [13]. Currently, it is one of most frequently used desensitising agents, since the American Dental Association accepted it in 1986 [14]. Its mechanism of treatment action is believed to involve depolarising the cellular membrane of the nerve terminal and, hence, decreasing the nerve response [12]. The efficacy of potassium nitrate in both self-applied toothpastes and a professionally applied solution has been observed in clinical trials [13,15]; hence, it has been used as a conventional method in managing dentine hypersensitivity. However, studies have reported conflicting results, and the efficacy of potassium nitrate in reducing dentine sensitivity has recently been questioned [11].

SDF is used as a professionally applied desensitising and caries-arresting agent [16]. The United States Food and Drug Administration cleared SDF in 2014 to treat dentine hypersensitivity [17]. A study demonstrated that SDF occluded the dentinal tubules on the exposed dentine surface [18]. This explained its desensitising effect. However, there are limited well-designed clinical trials that investigate the effectiveness of SDF in reducing dentine hypersensitivity in older adults [19,20].

## 2. Objective

This study’s objective is to evaluate the desensitising effect of the topical application of 38% SDF solution on the exposed root surfaces of hypersensitive teeth in older Chinese adults.

## 3. Hypothesis

The hypothesis under investigation is that the topical application of 38% SDF solution is more effective than 5% potassium nitrate solution in desensitising hypersensitive teeth with an exposed root surface in older Chinese adults.

## 4. Methods/Design

### 4.1. Trial Design

This is a randomised, single-centre, double-blind clinical trial with two parallel arms. The trial’s design and reporting follows the Standard Protocol Items: Recommendations for Interventional Trials (SPIRIT) statement (Supplementary Material S1) [21].

### 4.2. Participant Timeline

A SPIRIT figure is used to describe the trial schedule of enrolment, intervention and assessment and is presented in Figure 1.

### 4.3. Study Setting

This clinical trial will be conducted in the Clinical Research Centre in the Faculty of Dentistry of the University of Hong Kong.

### 4.4. Participants

We will recruit healthy older adults, aged 65 or older, with dentine hypersensitivity. They should have no known or suspected allergies to the study ingredients or materials, and they should have all active dental diseases under control. Older adults will be excluded if they have been using any desensitising agent within the past month, have major systemic diseases such as cancer, have dentine hypersensitivity due to other dental conditions such as caries or cannot give written consent. A research assistant will call older adults via phone. Those who have experienced symptoms of dentine hypersensitivity (such as sharp pain when eating cold or sour food) within 4 weeks will be invited for a dental examination. Figure 2 shows the consort flow diagram.

### 4.5. Informed Consent

A research assistant will explain the study’s purpose and procedures to all potential older adults who meet the inclusion criteria and the assistant will obtain their written consent (Supplementary Material S2).

### 4.6. Baseline and Follow-Up Clinical Examinations

A trained dentist will perform baseline and follow-up clinical examinations and assessments of dentine hypersensitivity. We will collect demographic background information, such as age, sex, dietary habit and denture use. A research assistant will measure the compressed cold air pressure and temperature of all the 3-in-1 syringes to be used in the Clinical Research Centre via a digital pressure indicator (DPI 2600847b) and a thermocouple digital sensor/thermometer (KM2013c) before all baseline and follow-up clinical examinations. The acceptable ranges of compressed cold pressure and temperature are 65 to 75 psi and 18 to 24 °C, respectively [8].

A trained examiner will measure the oral hygiene status of the older adults via the visible plaque index (VPI) and will record it as 0 for the absence of plaque and 1 for the presence of plaque [22]. The trained examiner will dry and clean all tooth surfaces with a piece of gauze. Cotton rolls will isolate hypersensitive teeth due to exposed root surface. They will then be assessed for dentine hypersensitivity using compressed air delivered from a 3-in-1 syringe placed approximately 1 cm away from and perpendicular to the exposed root surface for 5 s [23]. The older adult will give a self-perceived sensitivity score (SS) from 0 to 10 to all teeth under assessment for dentine hypersensitivity [8]. An SS of 0 will indicate no discomfort, whereas an SS of 10 will indicate maximum pain causing great distress to the subject (Figure 3) [24].

We will exclude older adults with a pre-treatment SS of less than 8 from this study. For each older adult, we will select the most hypersensitive tooth (the highest SS) due to exposed root surface for the assessment of dentine hypersensitivity in follow-up visits. A dental periodontal graduated probe at the nearest mm will measure the maximum amount of gingival recession of the selected hypersensitive tooth. The same trained examiner will perform the clinical examination and assessment of dentine hypersensitivity immediately after treatment and at 4-week and 8-week follow-up visits, using the same tools and procedures as in the baseline examination. We will re-examine 10% of the older adults later on the same day to assess the intra-examiner agreement at the baseline and follow-up examinations. To promote the follow-up rate, a research assistant will remind all older adults of their follow-up appointment schedule. If they are absent at the follow-up visit, another timeslot will be provided within the same week.

### 4.7. Intervention

After the baseline or follow-up clinical examinations, the eligible older adults will receive either 38% SDF solution (Saforide 38%, Morita, Osaka, Japan) or 5% potassium nitrate solution (Potassium Nitrate, Sigma-Aldrich, Darmstadt, Germany) on the exposed root surface of the selected hypersensitive tooth. If the adjacent tooth or teeth are also hypersensitive, the adjacent tooth or teeth will also receive therapy. An independent operator will dry the selected hypersensitive tooth and use a micro-brush to apply either 38% SDF solution or 5% potassium nitrate solution for 60 s [25], according to the assigned treatment group, on the exposed root surface. The SDF and potassium nitrate will be applied at baseline and at the 4-week follow-up visit after clinical examination. All eligible older adults will receive dietary advice, standardised oral hygiene instruction, a toothbrush and a regular fluoridated toothpaste (1450 ppm) after baseline examination until the end of the study period. We will instruct all older adults not to eat or drink for 30 min after SDF or potassium nitrate application. Because a dentist will professionally apply the intervention, there will be no concern regarding adherence to the intervention for both groups. Applying SDF or potassium nitrate solution will not affect the participants’ usual care pathways, such as medication use. They are prohibited from receiving other dental treatments for dentine hypersensitivity during the study period. In addition, they must follow the oral hygiene instruction received at the baseline visit.

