### 4.13. Data Analysis

We will apply the statistical software SAS for Windows (SAS Institute Inc., Cary, NC, USA) and SPSS for Windows (IBM Corporation, Armonk, NY, USA) for data analyses. The data will be assessed for a normal distribution using the Shapiro–Wilk test for normality. A chi-squared test will be used to determine the difference in distribution of gender and tooth type between the 2 groups. A Mann–Whitney U test will be used to study the pre- and post-treatment SS and the reduction in SS of the treatment group if these data are not normally distributed, whereas a t-test will be used instead if these data are normally distributed. We will report the medians and interquartile ranges for all of the continuous variables to provide information on the data distribution. All statistical tests will be 2-tailed, and the significance level will be set at 0.05. This study will use the intention-to-treat principle for analysis. However, if the number of older adults who withdraw from the study is significantly different between test and positive control groups at the 8-week follow-up visit, we will use a per-protocol approach for analysis and only older adults who have completed the 8-week follow-up will be included in the results. We will also study independent variables, such as demographic background and VPI, which may modify the treatment effect.

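### The fallback per-protocol set in section 4.13 is a completers set: its only printed criterion is finishing week 8, and section 4.7 dismisses adherence although the second application depends on attending week 4

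*Protocol article*

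**What the plan says.** All references are to the protocol article.

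- **Regimen (4.7).** There are two applications: "The SDF and potassium nitrate will be applied at baseline and at the 4-week follow-up visit after clinical examination".
- **Adherence (4.7).** "Because a dentist will professionally apply the intervention, there will be no concern regarding adherence to the intervention for both groups".
- **Conditions that rest on the participant (4.7).** "We will instruct all older adults not to eat or drink for 30 min after SDF or potassium nitrate application"; "They are prohibited from receiving other dental treatments for dentine hypersensitivity during the study period"; and "they must follow the oral hygiene instruction received at the baseline visit".
- **Missed visits (4.6).** A research assistant sends reminders, and "If they are absent at the follow-up visit, another timeslot will be provided within the same week". Nothing is stated beyond that.
- **Primary outcome (4.10).** Change in sensitivity score (SS) from baseline to week 8, that is, after both planned applications.
- **Analysis sets (4.13).** Intention-to-treat is the default. If the numbers withdrawing differ significantly between the arms at week 8, "we will use a per-protocol approach for analysis and only older adults who have completed the 8-week follow-up will be included in the results".
- **Planned loss (4.11).** 10% dropout; 148 participants, 74 per group.

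**The concern.** A per-protocol result is normally read as the effect in people who received the treatment as planned and did not depart from the protocol in ways that matter. Here the plan is two applications and no other hypersensitivity treatment. The criterion printed in 4.13 tests neither. It tests only whether the participant was still present at week 8.

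This matters because the set is not offered as a side analysis. When the withdrawal condition is met, it takes the place of intention-to-treat. The headline result would then be a completers analysis under a per-protocol label, and readers could take it as the effect of two applications without outside treatment.

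The adherence sentence in 4.7 compounds the problem. Having a dentist apply the agent secures correct delivery at a visit that takes place. It does not secure the visit, and the second of the two applications depends on one.

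**Working it through.** **Step 1. Set the printed criterion against the protocol's own requirements.**

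| Participant (all attend week 8) | Departs from 4.7? | In the set printed in 4.13? |
|---|---|---|
| Both applications, no outside treatment | No | Yes |
| Absent at week 4 and at the replacement slot | Yes, one application of two | Yes |
| Attends week 4 but declines the application | Yes, one application of two | Yes |
| Both applications, prohibited outside treatment | Yes | Yes |

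The criterion "only older adults who have completed the 8-week follow-up will be included in the results" does not separate the first row from the other three. Section 4.9 removes participants who ask to be unblinded, but that is a different rule and covers none of these rows.

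**Step 2. Set the adherence sentence against 4.6 and 4.7.** The reason given is that a dentist applies the agent. One of the two applications falls at a follow-up visit, and 4.6 provides reminders and a replacement slot because some visits will be missed. The stated reason therefore supports correct delivery when a participant attends, and no more.

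**Step 3. Check that the sample size is not at issue.** Inputs from 4.11 and 4.13: change in SS of 52% against 40% (difference 12 points), standard deviations 22% and 23%, two-sided alpha 0.05, power 0.80, dropout 10%, Mann–Whitney test.

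- Pooled SD = √((22² + 23²)/2) = 22.51; d = 12/22.51 = 0.533.
- Two-sided Mann–Whitney by the asymptotic relative efficiency (ARE) method, with the minimum ARE of 0.864: 66 per arm (power 0.806).
- 66/0.90 = 73.3, rounded up to 74 per arm; 2 × 74 = 148.

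The stated figure is reproduced exactly. The 10% allowance covers participants who are lost, not completers who received one application.

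**Step 4. Illustrate possible dilution, on assumptions only.** The documents give neither the share *f* of completers who miss the second application nor the share *r* of the between-arm effect that one application keeps. With assumed values, the diluted difference is 12 × (1 − f(1 − r)). The standard error of the difference with 66 completers per arm is 22.51 × √(2/66) = 3.92 points. Power uses 66 per arm and the minimum ARE.

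| f | r | Difference (points) | Shift (points) | Shift / SE | Power |
|---|---|---|---|---|---|
| 0 | – | 12.0 | 0 | 0 | 0.806 |
| 5% | 0.5 | 11.7 | 0.3 | 0.08 | 0.786 |
| 10% | 0.5 | 11.4 | 0.6 | 0.15 | 0.765 |
| 20% | 0.5 | 10.8 | 1.2 | 0.31 | 0.719 |
| 10% | 0 | 10.8 | 1.2 | 0.31 | 0.719 |
| 20% | 0 | 9.6 | 2.4 | 0.61 | 0.617 |

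An *f* of 10% already equals the trial's whole dropout allowance, although it counts only people who miss week 4 and return at week 8. The upper rows are the more plausible, and none of them is an estimate.

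**The case against.** The strongest reply has four parts.

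*The adherence sentence is about home use.* The background contrasts agents that patients apply daily with agents that clinicians apply, so the sentence may mean only that there is no self-application to monitor. Attendance is dealt with separately in 4.6. This is a fair reading of the intent, and removing the sentence would by itself change no result. As worded, however, it covers adherence to the intervention as a whole.

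*Section 4.13 can be read as a per-protocol approach and, in addition, completion of week 8, with detailed criteria left to a fuller document.* It is true that no sentence says outright that participants with one application or outside treatment count as compliant; that follows from completion being the only criterion printed. But this is a stated rule, not a silence, and followed as written it gives a completers set.

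*The set is a conditional fallback.* This stands. Intention-to-treat is the default, and under it including participants who had one application is intended and is no bias.

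*A stricter set brings its own bias.* This also stands. Requiring both applications selects on events after randomisation. If participants miss week 4 because relief was poor, the selection is related to outcome.

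Three stronger readings are tempting but unsupported. A reader might infer that a late week-8 visit becomes a missing primary outcome; 4.6 offers a slot in the same week but does not say that a later score is refused. A reader might infer crossover between arms; none is described, and the issue is outside treatment only. A reader might treat a 5–10% dilution as a finding; it rests wholly on assumed rates.

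**Conclusion.** The point holds as a matter of definition and labelling with consequences for the reported result. The set that 4.13 calls per-protocol is, by its only printed criterion, a completers set, and in the stated circumstance it replaces intention-to-treat. The claim in 4.7 that adherence raises no concern does not hold for an application that depends on attending week 4.

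The conclusion rests on reading the printed criterion as the operative one; a fuller document could add to it, but would have to depart from this text to do so. The numerical effect cannot be derived from the documents. With half the effect kept and 10–20% missing the second application, both assumed, the shift is 0.6 to 1.2 points against a standard error of about 3.9. Sample size, alpha and the default analysis are not in error.

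**What to change.** 1. In 4.13, keep intention-to-treat as the primary analysis in all cases, whatever the pattern of withdrawal.
2. Report per-protocol only as a supplement, defined as both assigned applications received, no prohibited hypersensitivity treatment, and week-8 SS measured. If the present criterion is kept, label the set completers.
3. Record for each participant whether the week-4 application was given, and any prohibited treatment.
4. State that week-8 SS is measured whether or not the week-4 application was given.
5. In 4.7, limit the adherence sentence to correct delivery at attended visits.

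The cost is wording in 4.7 and 4.13, a line on continued follow-up, and one or two items on the visit form. The number of participants and alpha do not change. The supplementary set will be smaller and is selected on post-randomisation events, so it must not carry the main conclusion.

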### 4.8. Randomisation, Treatment Group Allocation and Allocation Concealment

A research assistant will randomly allocate eligible older adults who have at least 1 hypersensitive tooth with an SS of 8 or more due to exposed root surface into 2 intervention groups with a block randomisation of 6 and with a 1:1 ratio. A statistician will generate a random number sequence in a computer. The 2 intervention groups are as follows:SDF (test) participants will receive topical application of 38% SDF solution on the exposed root surface of the most hypersensitive tooth every 4 weeks;Potassium nitrate (positive control) participants will receive topical application of 5% potassium nitrate solution on the exposed root surface of the most hypersensitive tooth every 4 weeks.

There will be no negative control group for ethical reasons. A research assistant will keep the random number sequence in opaque sealed envelopes and conceal the allocation sequence until interventions are assigned.

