### 4.9. Blinding

The examiner and the participating older adults will be blinded to the group allocation throughout the study. An independent operator will apply SDF or potassium nitrate solution after clinical examination. If the older adult requests the treatment history, unblinding is allowed. An unblinded research assistant will disclose treatment allocation to that older adult, who will then be excluded from the study.

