## 6. Trial Status

This clinical trial was registered on ClinicalTrials.gov (United States) under the registration number NCT05392868 on 22 May 2022. This protocol is version 1, written on 21 July 2022. Participant recruitment began on 1 September 2022 and this study is expected to end on 30 April 2023.

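### One fixed, disclosed block size of 6 lets anyone who knows the earlier assignments deduce about a quarter of allocations; the route to bias is narrow and the remedy cheap

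*Protocol article*

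**What the plan says.** Section 4.8 of the protocol article assigns participants to the two arms "with a block randomisation of 6 and with a 1:1 ratio". The abstract says the same: participants are "randomly allocated into two groups using a block randomisation of six". Neither place mentions varying block sizes. Section 4.1 describes the trial as single-centre, and no stratification factor is named.

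Concealment is described in 4.8: "A research assistant will keep the random number sequence in opaque sealed envelopes and conceal the allocation sequence until interventions are assigned".

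Section 4.9 names the examiner and the participants as blinded. It also says that "An unblinded research assistant will disclose treatment allocation to that older adult", so at least one assistant knows the assignments. A separate operator applies the assigned agent (4.7 and 4.9) and is not named among those blinded.

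The article uses the same term, a research assistant, for whoever phones candidates (4.4), takes consent (4.5), allocates and keeps the envelopes (4.8). It does not say whether these are the same or different people.

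On timing, section 6 says: "Participant recruitment began on 1 September 2022 and this study is expected to end on 30 April 2023".

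**The concern.** A sealed envelope stops someone from reading the next assignment. It does not stop someone from working it out. With a constant block size and 1:1 allocation, once one arm has used its three places in a block, every remaining place in that block belongs to the other arm. Anyone who keeps a tally of past assignments knows those places in advance. Blinding the examiner does not help here, because the examiner is not described as choosing who is phoned, consented or booked next.

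At stake is the comparability of the arms at entry. The primary outcome (4.10) is the change in a self-reported pain score. If a staff member knew the next assignment and let it influence who was invited, consented or booked, or in what order, the arms could differ in ways that move that score.

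**Working it through.** **Inputs from the article.** Block of 6 at 1:1, so 3 + 3 per block (4.8 and abstract); one centre, no stated strata (4.1); N = 148 (4.11). **Assumption.** The observer knows all earlier assignments and where the sequence started.

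**The plan's own figure.** The article gives no predictability figure; the only related number is N. It reproduces: pooled SD = √((22² + 23²)/2) = 22.51; d = (52 − 40)/22.51 = 0.533; a two-sided Mann–Whitney test at 0.05 with power 0.80 and the minimum asymptotic relative efficiency (0.864) needs 66 per arm; 66/0.90 = 73.3, so 74 per arm and 148 in total. The block size does not enter this calculation.

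**Certain allocations, fixed block of 6.** There are C(6,3) = 20 equally likely blocks. An allocation is certain when one arm has already used its three places.

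- Position 4: the first three are all one arm, 2/20 = 0.10.
- Position 5: the first four split 3–1, 2 × C(4,3)/20 = 8/20 = 0.40.
- Position 6: always, 1.00.

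Expected number per block = 0.10 + 0.40 + 1.00 = 1.5, and 1.5/6 = 25.0%. Over 148 participants there are 24 full blocks and 4 further places: 24 × 1.5 + 0.10 = 36.1, and 36.1/148 = 24.4%.

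**Best-guess rate, fixed block of 6.** The observer always guesses the arm with more places left. The chance of being right, by position:

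| Position | Calculation | Result |
|---|---|---|
| 1 | no information | 0.50 |
| 2 | 3/5 | 0.60 |
| 3 | 0.4 × 3/4 + 0.6 × 1/2 | 0.60 |
| 4 | 0.1 × 1 + 0.9 × 2/3 | 0.70 |
| 5 | 0.4 × 1 + 0.6 × 1/2 | 0.70 |
| 6 | always known | 1.00 |

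Sum = 4.10, and 4.10/6 = 68.3%, against 50% without blocking.

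**Randomly varying sizes.** These were simulated over 148 participants. The observer knows the set of sizes and all earlier assignments, but not the block boundaries, and updates by Bayes' rule.

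| Block sizes | Certain | Best guess right |
|---|---|---|
| 6 (fixed) | about 24–25% | about 68% |
| 4, 6 | about 6% | about 69% |
| 4, 6, 8 | about 2% | about 68% |
| 6, 8, 10 | about 1.6–1.7% | about 66% |
| 8, 10, 12 | about 1.3% | about 65% |

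**Reading the two columns together.** Varying the sizes removes most of the certainty but little of the guessing. Correct guesses above chance, per 148 participants, are (0.683 − 0.5) × 148 ≈ 27 with a fixed 6 and (0.663 − 0.5) × 148 ≈ 24 with 6, 8 and 10.

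**The case against.** **The trial's own sequence limits what foreknowledge can do.** This is the strongest reply, and it largely stands. Candidates are phoned on the basis of symptoms and give consent; a blinded examiner then gives the air blast, the participant scores it, and only those with SS of 8 or more are allocated. Whoever phones or consents cannot know who will reach 8, so cannot reliably steer a chosen person into a predicted place. The entry score comes from a blinded participant and is recorded by a blinded examiner, so staff foreknowledge does not set it. What remains is influence over who is invited, consented or booked, and in what order.

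**The role overlap is not stated.** A reader might infer that one research assistant phones, consents, allocates and also knows the assignments. The article does not say so: section 4.12 shows there are at least two assistants, and specifying one as unblinded suggests that others may be blinded. The operator has no stated recruiting role. A condensed article may leave role separation to the full protocol. This also stands, but the article does not rule the overlap out, and the fixed block size is something it states, not something it omits.

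**The fix barely lowers the guess rate.** True, as the table shows. The gain is confined to certain predictions.

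**Selection could be handled in analysis.** Partly. Baseline SS, plaque index, gingival recession and demographic data are recorded, so measured imbalance can be seen and adjusted for. A claim that nothing could be corrected would be too strong; it is selection on unmeasured characteristics that cannot be.

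**Publication adds little.** Site staff would be expected to know their own protocol. The article's publication date is not in the text; it shows only that recruitment had begun and the study end was still expected.

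**Conclusion.** The point holds as a minor-to-moderate vulnerability. A fixed, disclosed block of 6 makes 25% of allocations certain to anyone who knows the earlier ones (about 36 of 148 over a whole trial) and gives a best-guess rate of 68.3%. Sealed envelopes and a blinded examiner do not prevent this deduction.

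The conclusion rests on three assumptions: the sequence is a single unstratified list, as the text implies; some staff member knows the running tally; and that person has some say in who is invited, consented or booked, or in what order. The article makes the second likely, since an unblinded assistant exists and the operator is not listed as blinded. It leaves the third open.

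A reader might go further and conclude that allocation in this trial was in fact anticipated or that its result is biased. Nothing in the article supports that. Nor should the figure of 36 be read as what a change now would save: recruitment started on 1 September 2022, and a study end of 30 April 2023 with 8 weeks of follow-up implies that randomisation closes by about 5 March 2023. A change helps only those not yet randomised, and the article does not say how many they are.

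**What to change.** Finish the current block of 6. Then have the statistician generate a continuation list for the remaining participants with randomly varying block sizes, for example 6, 8 and 10. Keep the sizes in a document closed to all staff who recruit, consent, allocate, treat or examine. Allocations already made stand. In 4.8, replace the block size with wording such as: *permuted blocks of randomly varying size, not disclosed to site staff*.

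The cost is a new list, new envelopes and a short amendment. The final imbalance between arms could be up to 10/2 = 5. If the current block were abandoned part-way it could be 3 + 5 = 8, which is why that block should be completed first. Even at 8, with 78 and 70 participants, the balanced-equivalent total is 4 × 78 × 70/148 = 147.6, so the effect on power is negligible.

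There is no benefit for participants already randomised. For them, the trial report should state the fixed, disclosed block size as a limitation. If recruitment is already complete, that statement is all that remains to be done.
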